### Data collection, processing, and quality control

In Groups 2–6 and the natural history cohort, outcomes information will be collected from participants by telephone interviewers unaware of treatment group at baseline, week 5 (end of primary treatment period), week 12 (end of secondary treatment period), and week 26 (Table
3). Participants in Group 1 will be interviewed by telephone interviewers unaware of treatment group at baseline, week 5 (end of waitlist period), week 10 (end of primary treatment period), 17 (comparable to end of other groups secondary treatment period), and week 31. We will also ask participants in Groups 2 through 6 and the natural history cohort to complete a short internet survey at 10, 16, 20, and 39 weeks post-randomization. Participants in Group 1 will be asked to complete a short internet survey at weeks 15, 21, and 25 weeks. This will allow us to more precisely characterize the persistence of any treatment benefits of the initial dose as well as of the 6-week booster dose. Results of follow-up data from internet questionnaires or telephone interviews will not be seen by the massage therapists.

We will attempt to obtain outcomes data from all participants in the trial and the natural history cohort, including those who fail to appear for any treatments, those who subsequently discontinue treatments, those who discontinue enrollment in the health plan, and those who move away. Baseline and follow-up telephone interviews will be conducted using Computer-Assisted Telephone Interviews (CATI). At the 5, 12 and 26 week follow-up interviews, the interviewers will be unaware of the participants’ treatment assignments. To maintain assessor masking for questions relevant for all study participants, questions focused on the massage treatment (when relevant) will not be asked until all other questions have been completed and stored in the CATI database. Baseline interview data will be collected before randomization to treatment group.

We will collect information on recruitment, randomization, and treatment processes so we can report patient flow according to the CONSORT guidelines
[29,30]. Specifically, we will record the number of invitation brochures sent, the number of responses received, the resolution of these responses (ineligible, refused, eligible and randomized, other), the number of participants in all groups who received at least one massage treatment, the number of visits made, the number of participants providing follow-up data by group at each follow-up, the number of participants completing the trial, and the number of withdrawals due to: ineffective treatment, adverse experiences, loss to follow-up, or other causes.

We will create weekly reports to monitor recruitment, visit adherence, and follow-up interviews for all time points. This will allow us to identify and resolve any difficulties that arise in the course of the trial.

For all visits, the massage therapists will use Visit Forms to record important clinical and research information. These forms will identify participants only by their initials and Study ID numbers. The Initial Visit Form will include clinically useful information such as primary and secondary problems identified, medical history, the assessments performed and their findings, treatment techniques used, and their anatomic location. The Initial and Follow-up Visit Forms will be similar, except only the former will include medical history while only the latter will include an assessment of progress since the last visit.

Specific quality control procedures for data collection will be developed during the start-up phase of the trial. These will include procedures to ensure that the trial is running smoothly (e.g., randomization is proceeding as planned, recruitment is on schedule, data collection forms are accurately entered into databases, the computerized interviewing system is storing data correctly). The computerized interviewing programs will contain range and logic checks. Prior to recruitment, all data systems will be tested with imaginary participants. Data will be examined for completeness using computer programs developed specifically for that purpose. In addition, we will test all analytic programs to ensure that the analyses are accurate.

Computer files with patient names will be password protected with access restricted to staff using this information to recruit patients, obtain follow-up data, and interact with any patients reporting adverse events. During treatment, clinic charts containing Visit Forms (identified by Study ID numbers and patient initials) will be stored in locked filing cabinets in the research clinic. After being audited to ensure adherence to the protocol, completed visit charts will have initials removed, and again stored in locked filing cabinets accessible only to study personnel.

### Protection of human subjects and assessment of safety

#### Protection of human subjects

The study was approved by Group Health’s institutional review board, the Human Subjects Research Committee (IRB Number 00000668), which serves as the ethics committee. The study will be carried out in compliance with the Helsinki Declaration

#### Adverse events

Participants will be asked about adverse experiences at each clinic visit and during the 5 and 12-week telephone interviews. We will define an adverse experience as any unfavorable and unintended sign, symptom or disease temporally associated with the use of the massage treatments that could reasonably be related to the procedure. Because massage has relatively short-term physiological effects, we will not report adverse events that begin more than two weeks after a participant’s final massage treatment (or more than 14 weeks after randomization for the usual care control group). In addition, we will capture information about any Serious Adverse Events (i.e., any adverse event occurring during treatment that results in any of the following outcomes: death, a life-threatening adverse event, inpatient hospitalization or prolongation of existing hospitalization, a persistent or significant disability/incapacity, a congenital anomaly/birth defect, or cancer) regardless of when they occurred.

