### Natural history cohort study

In addition to inclusion of a 4-week wait list control group, we will recruit a separate cohort of 50 patients with chronic neck pain, who will serve as a natural history comparison group for the 9 month follow-up period. We decided to include a separate natural history group because we did not believe we could recruit and retain individuals randomized to a 9 month control group in the context of the dosing trial, where all other groups would received from 4 to 18 h of massage within the first 12 weeks of the study. We will recruit members for the natural history cohort who meet the same inclusion and exclusion criteria as the dosing study participants over the same time period. However, the natural history cohort will be recruited from the Puget Sound region by selecting zipcodes outside of the dosing study recruitment region centered in Seattle. We will recruit participants using the same procedures we use for the dosing trial but we will modify our telephone eligibility screening questions to reflect the lesser requirements of participating in the Natural History Control Group (i.e., we will not ask about availability for massage treatments, transportation to our downtown clinic location, ability to get on and off of a massage table, use of a wheelchair, etc.). We will also not require an in-person pre-randomization visit. After obtaining oral consent and collecting baseline data we will follow cohort members for 9 months asking them to complete the series of telephone interviews and internet questionnaires given to members of Groups 2 to 6. These questionnaires will be virtually identical to those of the trial participants, but will omit all references to adverse events and other effects of the study treatments.

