**TREATMENT-RELATED INFORMATION**					
Adverse experiences attributed to treatment		x	x		
Home practice recommendations		x	x		

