		**Week number**																									
**Schedule of treatments and assessments**	**Pre-study and randomization**	**Wk 1**	**Wk 2**	**Wk 3**	**Wk 4**	**Wk 5**	**Wk 6**	**Wk 7**	**Wk 8**	**Wk 9**	**Wk 10**	**Wk 11**	**Wk 12**	**Wk 13-14**	**Wk 15**	**Wk 16**	**Wk 17**	**Wk 18-19**	**Wk 20**	**Wk 21**	**Wk 22-24**	**Wk 25**	**Wk 26**	**Wk 27-30**	**Wk 31**	**Wk 32-38**	**Wk 39**
Wait list Control (Group 1)		y	y	y	y																						
Primary Treatment Period																											
(Groups 2-6)		z	z	z	z																						
Primary Treatment Period																											
(Group 1)							y	y	y	y																	
Secondary Treatment Period																											
(50% of Groups 2 - 6)							z	z	z	z	z	z															
Informed Consent																											
	x, y																										
Baseline Characteristics	x, y					y																					
Primary Outcomes	x, y					x, y					x, y	x			y	x	y		x	y		y	x		y		x
Secondary Outcomes	x, y					x, y					y	x					y						x		y		
Adverse Events						z					y	z															
Potential Co-interventions	x, y					x, y					y	x					y						x		y		
Other Measures	x, y					x, y					y	x					y						x		y		

Legend: y=Group 1; x=Groups 2-6 & Natural History Controls; z=Group 2 - 6 only;=Internet survey.

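### The adverse-event window names a control arm the trial does not have, the text and tables disagree on who is asked and by what criterion, and Table 3 leaves no untreated rate for non-serious symptoms other than neck worsening

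*Protocol article*

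**What the plan says.** **Window.** Under Adverse events, the protocol article says of massage recipients: "we will not report adverse events that begin more than two weeks after a participant’s final massage treatment". In the same sentence it sets a separate limit for controls: "or more than 14 weeks after randomization for the usual care control group".

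**Who is asked, in the text.** The same section opens: "Participants will be asked about adverse experiences at each clinic visit and during the 5 and 12-week telephone interviews". It names no group.

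**Who is asked, in the tables.** Table 2 has a row headed "Adverse experiences attributed to treatment", ticked at 5 and 12 weeks, with no group restriction on the row. Table 3 uses the key "Legend: y=Group 1; x=Groups 2-6 & Natural History Controls; z=Group 2 - 6 only". Its Adverse Events row carries z at week 5, y at week 10 and z again around the end of the secondary treatment period. There is no x anywhere in the row and no y at week 5.

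**Natural history cohort.** Its questionnaires match those of the trial "but will omit all references to adverse events and other effects of the study treatments".

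**What counts.** The Adverse events section defines the event as one "temporally associated with the use of the massage treatments that could reasonably be related to the procedure". Table 2 makes attribution to treatment part of the item. The section Secondary and other outcomes speaks of adverse experiences of any kind, at clinic visits and at the two interviews.

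**The concern.** The control-group clause cannot be applied as written, because no randomised or non-randomised group bears that name and its 14 weeks suit neither actual comparator. It also presupposes that some control group reports adverse events. Table 3 and the natural history section schedule no such reporting from anyone who is still untreated.

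Headache, soreness and similar complaints may occur in people with chronic neck pain whether or not they are massaged. If only massage recipients are asked, a count of such complaints cannot be set against a background rate, and relatedness has to be settled by opinion. The waitlist is the randomised group that could supply that background, and it already has a masked telephone interview at week 5.

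The three criteria matter separately. A participant's own attribution, a judgement of reasonable relatedness, and an enquiry about any adverse experience will not return the same events. Participants also know whether they have had massage.

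**Working it through.** The plan states no figure on this point, so there is none to reproduce. The check has three parts: a reading of the schedule, the window arithmetic, and an illustration of what the missing comparison could deliver.

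**1. Who is asked while untreated**

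| Source | Week 5, Group 1 | Week 5, Groups 2–6 | Natural history cohort |
|---|---|---|---|
| Adverse events, opening sentence | not excluded | asked | not excluded |
| Table 2 | not excluded | asked | not excluded |
| Table 3 | not asked (first entry week 10) | asked | not asked |
| Natural history cohort study | – | – | explicitly left out |

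The section Schedule of assessments treats Group 1 in weeks 5 to 9, so its week-10 entry follows massage. Taking Table 3 as it stands, untreated participants with a scheduled enquiry number 0 of 38 in the waitlist and 0 of 50 in the natural history cohort.

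**2. Which group a 14-week limit fits** (last treatment week plus two)

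- Groups 2–6 with additional treatment: 12 + 2 = 14. This matches, but these participants are massage recipients.
- Groups 2–6 without additional treatment: 4 + 2 = 6.
- Group 1: 9 + 2 = 11. By week 14 it has been massaged and is no longer an untreated control.
- Natural history cohort: not asked at all.

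The figure therefore appears to be carried over from the treated groups' calendar and describes no control group.

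**3. What asking the waitlist at week 5 would give**

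Inputs: 34 followed per group (section Sample size and the detectable difference), so 34 waitlist v 5 × 34 = 170 massage. The documents give no adverse-event rates, so those below are assumptions.

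Half-width of the 95% interval = 1.96 × √[p₀(1 − p₀)/34 + p₁(1 − p₁)/170]

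- 20% v 40%: 1.96 × √(0.16/34 + 0.24/170) = 1.96 × 0.0782 = 0.153, about 15 points.
- 30% v 50%: 1.96 × √(0.21/34 + 0.25/170) = 1.96 × 0.0874 = 0.171, about 17 points.

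Power at two-sided 0.05 = Φ[(Δ − 1.96 × SE₀)/SE₁], with SE₀ from the pooled rate and SE₁ from the separate rates:

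| Assumed untreated rate | 10-point excess | 20-point excess |
|---|---|---|
| 5% | 29% | 83% |
| 10% | 24% | 72% |
| 20% | 20% | 61% |

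A large excess could be seen and a small one could not. Exact 95% intervals for the untreated rate alone would also be wide: 2/34 gives 0.7% to 19.7%, and 7/34 gives 8.7% to 37.9%.

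**The case against.** A reader might infer that harm cannot be judged against an untreated group at all. The documents do not support that. The Neck Disability Index, pain intensity and the global rating, which extends to marked worsening, are scheduled for every randomised group at week 5. A flare-up of the neck condition can therefore be compared with the waitlist under masked interview. The gap concerns other non-serious symptoms.

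A reader might also infer that events which participants do not blame on massage are lost. That is not shown either. The attribution wording is a row label in Table 2, the section on secondary outcomes describes a broader enquiry, and there is a separate enquiry at every clinic visit. The interview script is not shown. What stands is that the three descriptions differ.

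Nor does the missing rate disable the trial's decision rules. The optimal-dose definition and the stopping rule rest on serious adverse events, deaths from any cause go to the safety body within 7 days, and the five dose groups can still be compared with one another. The trial's declared aim is comparison of doses.

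It is also fair to say that Table 3 need not be the governing text. If the opening sentence of the Adverse events section governs, the waitlist is asked at week 5. In that case the table is wrong and the design is sound, so the finding is a contradiction to be resolved rather than a proven design decision. Finally, massage recipients are prompted at each visit and the waitlist is not, so even the proposed comparison would rest on self-report after unequal prompting.

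**Conclusion.** The point holds in limited form. Three things are established from the text alone: the 14-week clause fits no arm; the Adverse events section and Table 2 conflict with Table 3 and the natural history section on who is asked; and the criterion for an event is given in three different ways. If Table 3 is followed, no untreated comparison rate exists for non-serious symptoms other than neck worsening. That consequence comes from Table 3 and the natural history section. The mislabelled window is a separate drafting error.

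The size of what would be gained is modest: a massage-minus-waitlist difference with a 95% half-width of about 15 to 17 points, given 34 and 170 followed and the assumed rates above. The conclusion that the passages must be reconciled depends on none of those assumptions.

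**What to change.** 1. At the week-5 interview, ask all six groups one question free of attribution: any new or worsened symptom since baseline, with date of onset. Place it in the common block, which the plan already stores before massage-specific questions, so that masking is kept. Ask about attribution afterwards, in massage recipients only.
2. Report the massage-minus-waitlist difference from this interview item alone. Keep clinic-visit reports separate, because massage recipients are prompted more often.
3. Replace the clause about a usual care group with a window defined for Group 1: its untreated weeks up to the week-5 interview as control time, then the same post-massage window as the other groups.
4. State one criterion for an adverse experience and use it throughout the text. Align Tables 2 and 3 with it, and with one statement of who is asked and when, including that the natural history cohort is not asked if that remains the intention.

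The cost is one item in an interview already planned for Group 1, a corrected clause and two corrected tables. The drawbacks are more non-specific events to code and an estimate of limited precision.

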#### Safety monitoring

This trial will be monitored for safety by an independent Data Safety Monitoring Body (DSM Body) comprised of a biostatistician, primary care physician and massage therapist. The DSM Body will evaluate the adverse-experience data we will provide them every 6 months to protect the safety of the study participants. However, any massage related Serious Adverse Events or deaths for any reason will be reported to the DSMB within 7 days of discovery. Based on the observed adverse effects of the treatment under study, the DSM Body will make recommendations on a regular basis to the PI and the Office of Clinical and Regulatory Affairs at the National Center for Complementary and Alternative Medicine (NCCAM) regarding continuation, termination, or other modifications of the trial.

#### Stopping rules

The trial will be stopped only if the Data Safety Monitoring Body (DSMB) believes there is an unacceptable risk of serious adverse events in one or more of the treatment arms. In this case, the DSMB could decide to terminate one of the arms of the trial or the entire trial. Based on our previous research and on the small number of case reports, we believe the risk of serious adverse events related to massage therapy is low.

We are not proposing to perform an interim analysis for efficacy. Since sample size in each group is small (n=38 per group), we will need the total sample sizes to determine optimal dosing. We will, however, monitor adherence to the treatment visit schedule for each of the study arms. The DSMB will review the data every 6 months, but there will only be one formal stopping rule for a given treatment due to adherence issues halfway through recruitment after approximately 12 months of recruitment. Should we find that treatment adherence is particularly poor for one or more arms (i.e., ≥ 50% of a group attended less than 75% of the required visits), we will drop that arm and create a new randomization protocol that randomizes individuals in equal proportions to the remaining arms of the trial. We plan to follow-up all participants who were enrolled before stopping a given treatment group so that their data can be used in the per protocol analyses if deemed appropriate.

### Study calendar

The study calendar (Table
3) displays the timing of the activities with each participant in the trial and the natural history cohort.

### Statistical issues

#### Sample size and the detectable difference

Our sample was chosen to ensure adequate power to detect a significant difference between at least two of the 5 groups receiving a massage treatment in the first 4 weeks of the trial (and not just adequate power to find a difference between one or more of the treatment groups and the waitlist control group). This reflects the primary goal of the trial: to compare the effects of different doses of massage on neck-related disability, and not just to determine if massage is better than no-additional treatment (as in the waitlist control). Our primary outcome is the binary measure of clinically relevant improvement of at least 5 points on the Neck Disability Index (NDI) at 5 weeks compared to baseline NDI score
[31]. Based on findings in our pilot study, we assumed that 7% of the waitlist control group and 35% of Group 2 (60-min weekly treatment) would improve. We lack pilot data to estimate improvement rates in the other groups. Therefore, to permit sample size estimation, we will assume that treatment benefits will increase with the number of treatments given per week (for a fixed weekly dose) and with the number of minutes of massage per week. We assume a two–fold improvement from the lowest to the highest weekly dose (i.e., 60 to 180 min), based on the expectations of our consultant massage therapists. Table
4 summarizes our assumptions for both the NDI and neck bothersomeness score.

**Table 4 T4:** Assumptions for sample size calculations

**Group**	**Amount of massage (weekly dose)**	**Proportion with clinically relevant improvement on NDI (at least 5 point improvement)**	**Proportion with clinically relevant improvement on Bothersomeness score (≥ 30% improvement)**
1	Waitlist	0.07	0.10
2	60 min 1×/week (60 min)	0.35	0.48
3	30 min 2×/week (60 min)	0.40	0.55
4	60 min 2×/week (120 min)	0.55	0.65
5	30 min 3×/week (90 min)	0.60	0.70
6	60 min 3×/week (180 min)	0.70	0.80

To protect against multiple comparisons, we will use Fisher’s protected least significant difference approach. Although this approach has been shown to inadequately protect against the type I error rate for studies with more than 3 groups,
[32] we ran several simulations to test the type I error rate for our specific study design of 6 groups, with a binary outcome. We did this for sample sizes ranging from 30 to 40 and assuming an overall baseline improvement rate of either 0.07 or 0.50. We found that the type I error remained below 0.05 for all these situations. Following Fisher’s protected least significant approach, we will first use the omnibus Chi-Square test to test if there is any significant difference between all 6 groups and, if we find one, we will test for pairwise differences between groups. With 34 participants per group, we will have 97% power to find a significant difference between at least two of the 6 groups and 80% power to find a significant difference between Group 6 and Group 2, the treatment groups assumed to differ most in proportion of improvement. Assuming 10% loss to follow-up (as found in our pilot study and in our studies of back pain), we plan to recruit 38 participants in each group, for a total sample size of 228 in the trial.

Our other primary outcome is improvement in the Neck Pain Intensity Score of at least 30% from baseline, which reflects clinically important improvement
[33]. With a final sample size of 34 participants in each group we would have 99% power to find a significant difference between at least two of the 6 groups and 80% power to find a significant difference between Group 6 and Group 2 assuming improvement rates as outlined in Table
4. Therefore, we will have adequate power to assess both our primary outcomes.

It should be noted that both primary outcomes (function and symptoms) will be tested at each time point at the 0.05 level because they address separate scientific questions. Analyses of both outcomes at all follow-up times will be reported, imposing a more stringent requirement than simply reporting a sole significant
[34].

To address our second aim, the optimal duration of the treatment period, we will assess whether continuing treatment for another 6 weeks (60-min weekly massages for 6 weeks) improves outcomes in Groups 2–6. To simplify the power calculations, we focus on the 12 week response outcome and present those here. For the NDI (as a binary outcome), the power is 81%, when adjusting for group, assuming there are 34 participants in each of the 5 groups and assuming that, compared with those whose treatment stopped at 4 weeks, the additional proportion of each group improving at least 5 points from baseline after receiving 10 weeks of treatment is 0.2. The power is 88% for the binary neck pain intensity outcome, when adjusting for group and assuming that there are 34 patients in each of the 5 groups and assuming that, compared with those whose treatment stopped at 4 weeks, the additional proportion of each group improving at least 30% from baseline after receiving 10 weeks of treatment is 0.2.

Our power calculations are based on simple comparisons of the follow-up scores at a single point in time with adjustment for baseline values using logistic regression. We also plan to adjust for other baseline characteristics (e.g., age, gender). Inclusion of such baseline covariates can improve precision of the variance estimate and therefore increase power. For analyses of follow-up data for weeks 10 through 39 we will use generalized estimating equation methodology to handle within person correlation, possibly increasing our power at a given time point.

In summary, we have excellent power to detect clinically meaningful differences for both primary outcomes at both 5 and 12 weeks.

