##### Primary treatment period: primary study outcomes at 5 weeks

The primary analyses will look at binary outcomes: 1) improvement of at least 5 points from baseline Neck Disability Index score and 2) improvement of at least 30% from baseline on the pain intensity score. We will use the following logistic regression model,

(1.1)$$\;\begin{array}{cc} \text{logit}\left(Y_{i}\right) & =\beta_{0}+\beta_{1}Group2_{i}+\beta_{2}Group3_{i}\\ & \;+\beta_{3}Group4_{i}+\beta_{4}Group5_{i}\\ & \;+\beta_{5}Group6_{i}+\alpha {Ζ}_{i} \end{array}$$

where *GroupA*_*i*_ is an indicator variable of 1 if participant i was randomized to group A or 0 otherwise (A=2, 3, 4, 5, or 6) and Z_*i*_ is a vector of potential confounders including baseline outcome score. We will use the Fisher’s protected least significant approach to assess if there are any differences among the 6 Groups and then, if there is a significant difference, to assess if any pairwise differences are significant. It is also of interest to run a parametric model to evaluate a trend over the weekly dose while taking into account the number of visits. In standard dosing analyses, at the lower doses, the proportion of patients improves with increasing dose, but as the dose increases to some higher level, further improvement is attenuated and approaches a threshold (see Figure
2).

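### The below-0.05 type I error claimed for Fisher's protected LSD holds when all six groups are equal, not for dose-versus-dose tests once the waitlist is lower

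*Protocol article*

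**What the plan says.** The section on sample size and the detectable difference chooses the procedure: "To protect against multiple comparisons, we will use Fisher’s protected least significant difference approach". It concedes that the method is known to protect poorly with more than three groups, and answers that with simulations for this design: "We did this for sample sizes ranging from 30 to 40 and assuming an overall baseline improvement rate of either 0.07 or 0.50". The reported result is "We found that the type I error remained below 0.05 for all these situations".

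The procedure has two steps. First, "we will first use the omnibus Chi-Square test to test if there is any significant difference between all 6 groups". Second, "if we find one, we will test for pairwise differences between groups". No further adjustment of the pairwise tests is described. The section on primary outcomes at 5 weeks repeats the gate for Model 1.1: "assess if there are any differences among the 6 Groups and then, if there is a significant difference".

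The sample size section also says that the trial's main purpose is to compare doses with one another, beyond showing that massage beats the waitlist. Table 4 assumes 7% NDI improvement on waitlist and 35%, 40%, 55%, 60% and 70% in Groups 2–6. The second outcome has 10% on waitlist and 48–80% on massage.

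**The concern.** An omnibus gate protects the later pairwise tests only when all groups are truly equal. A false pairwise claim then needs a false omnibus rejection first, so the error cannot exceed the level of the gate. A single overall rate of 0.07 or 0.50 is that case.

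The known weakness of the method lies elsewhere. When one group really differs, it opens the gate for all the others. In this trial the waitlist is expected to differ greatly. If all doses work equally well and all beat the waitlist, the omnibus test rejects correctly, and ten dose-versus-dose tests follow at 0.05 each with little or no protection.

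The trial is meant to identify an optimal dose as a basis for later research. A chance difference between equally good doses could be taken forward as a dose effect under a stated error rate that does not apply to it.

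**Working it through.** **Inputs from the protocol article.** 34 evaluable participants per group; alpha 0.05 per outcome and time point; waitlist and dose rates from Table 4. **Assumptions.** Two-sided tests; the overall rate in the simulations is common to all six groups; Pearson tests unless another test is named.

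**Comparisons.** Six groups give 6 × 5 / 2 = 15 pairs, of which 5 × 4 / 2 = 10 are dose versus dose.

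**Gate.** X² = n Σ(p_g − p̄)² / [p̄(1 − p̄)], compared with the 5-df critical value 11.07. The results below come from Monte Carlo with at least 100,000 simulated trials per scenario. At 200,000 trials the standard error near 25% is √(0.25 × 0.75 / 200,000) = 0.1 percentage points.

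**Step 1: the plan's own figure.** With all six rates equal and 30 to 40 per group, the gate opens in 4.3–4.5% of trials at rate 0.07 and 4.9–5.0% at 0.50. That caps the pairwise error, so the plan's statement reproduces for the case it describes.

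**Step 2: why the waitlist opens the gate.** Put the true rates into X².
- Waitlist 0.07, doses 0.35: p̄ = (0.07 + 5 × 0.35) / 6 = 0.303. The sum of squares is 0.2333² + 5 × 0.0467² = 0.0653, so X² = 34 × 0.0653 / (0.303 × 0.697) ≈ 10.5.
- Waitlist 0.07, doses 0.50: p̄ = 0.428. The sum of squares is 0.3583² + 5 × 0.0717² = 0.1541, so X² = 34 × 0.1541 / (0.428 × 0.572) ≈ 21.4.

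Sampling variation adds about 5 (the degrees of freedom) on average. The typical statistic is therefore near 15.5 or 26.4 against 11.07, although the doses are identical.

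**Step 3: error among the 10 dose pairs when all five doses are equal.**

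| Outcome | Waitlist | Common dose rate | 6-group gate opens | At least one false dose pair |
|---|---|---|---|---|
| NDI | 0.07 | 0.35 | 79% | 29% |
| NDI | 0.07 | 0.40 | 92% | 30% |
| NDI | 0.07 | 0.50 | 99.5% | 25% |
| NDI | 0.07 | 0.60 | >99.9% | 30% |
| NDI | 0.07 | 0.70 | >99.9% | 29% |
| Pain | 0.10 | 0.48 | 96% | 25% |
| Pain | 0.10 | 0.65 | >99.9% | 31% |

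**Step 4: sensitivity.**
- Type of pairwise test: logistic Wald, the closest to Model 1.1, gives 24–29%; likelihood ratio 27–32%; Yates or Fisher exact 16–20%.
- Higher waitlist rate than planned: with doses at 0.35, the error is 14% at waitlist 0.20 and 9% at waitlist 0.25. With doses at 0.60 and waitlist 0.25 it is still 29%.
- Only Groups 4–6 equal (0.35, 0.40, 0.60, 0.60, 0.60): 13% among those three pairs.

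**Step 5: alternatives.**

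| | 6-group gate | Gate on Groups 2–6 | Closed testing in Groups 2–6 |
|---|---|---|---|
| Error, all five doses equal | 24–31% | about 5% | at most 5% |
| Error, four doses at 0.60, one at 0.35 | about 22% | about 17–18% | at most 5% |
| Error, Groups 4–6 plateau | 13% | about 12% | at most 5% |
| Group 6 v 2 power, NDI | about 83% | about 73% | about 61–63% |
| Group 6 v 2 power, pain | about 82% | about 65% | about 53–56% |

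Power uses the Table 4 rates. The plan states 80% for both outcomes, which the 6-group gate roughly reproduces. The omnibus test among the five doses alone has power of 79% (NDI) and 69% (pain).

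**The case against.** **The quoted sentence is true.** It is limited to the situations simulated, it reproduces there, and the article openly reports the method's weakness. A reader might infer that the authors reported a wrong number; the documents do not support that. What stands against the plan is the use of a correct result to set aside a warning that the result cannot test.

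**The reading of the simulations is an inference.** The article does not say in so many words that all six groups shared the rate. It describes no other scenario, however, and a single overall rate has no more natural meaning.

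**Equal doses are not the plan's expectation.** Table 4 has every dose different, so its planning scenario contains no true dose null. The flat pattern that the article itself discusses is a threshold effect across Groups 4–6, and there the error is about 13%, roughly half of the all-equal figure. This stands and belongs in the statement of size. Type I error still has to be judged under nulls, and both cases exceed 5%.

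**Strict control may be more than dose-finding needs.** The choice of dose also rests on adherence and serious adverse events, and Models 1.2 and 1.3 examine trend without pairwise tests. That is a fair argument for accepting uncontrolled pairwise tests if they are labelled so. It does not support claiming protection, which the article does for its primary analysis.

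**Conclusion.** The concern holds. The below-0.05 result covers six equal groups and does not extend to the dose-versus-dose comparisons that are the trial's main purpose. Under the plan's own waitlist rates, the chance of at least one false dose difference is about 24–30% for NDI (up to 31% for pain) if all five doses are equal and Pearson or logistic tests are used. It is 16–20% with conservative pairwise tests, and about 13% if only Groups 4–6 are equal. These figures are per outcome and rest on 34 per group. They fall if the waitlist improves much more than 7% while the doses stay near 35%.

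Three stronger readings are not supported:
- That the gate always opens. At a dose rate of 0.35, the only one with pilot data behind it, it opens in about 79% of trials.
- That a false dose finding is always more likely than one in four. At a dose rate of 0.50 the figure is just under that, and it is lower with exact tests or a partial plateau.
- That dropping the waitlist from the gate settles the matter. That restores 5% only when all five doses are equal.

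**What to change.** 1. State that the below-0.05 result applies only when all six groups have the same rate. Report simulations under partial nulls: waitlist lower, with all or some doses equal.
2. Gate the dose-versus-dose tests on a 4-df test among Groups 2–6 (H0: β1 = β2 = β3 = β4 = β5 in Model 1.1). Treat the five waitlist comparisons as a separate family.
3. Restate Group 6 versus Group 2 power as about 73% (NDI) and 65% (pain), and say that this gate gives 5% error only when all five doses are equal.
4. Decide whether strong control is wanted. If so, use closed testing within Groups 2–6 and state its power (about 61–63% and 53–56%). If not, describe the dose-pair tests as not familywise controlled.

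Items 1–3 need only analysis wording, new simulations and less favourable power figures. Item 4 is a real trade-off: keeping 80% power with strong control would need more participants.
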